### Cancer Prevention Social Media Campaign

The social media campaign will deliver 2 posts per day (n=approximately 720 posts) over 12 months, addressing cancer risk reduction, teaching digital and media literacy, encouraging family and friend communication, responding to misinformation, and highlighting community resources. The diverse content should be engaging and should avoid fatigue, but we will assess information overload and compare varying intervention durations (ie, 13, 26, 36, and 52 weeks).

#### Theoretical Approach to Social Media Intervention

We will adopt a multitheoretical approach to influencing rural emerging adults’ health behaviors. Social cognitive theory (SCT) [93] and self-determination theory (SDT) [94] will provide a framework and guide message development and measures of theoretical mediators, including cancer risk perceptions, self-efficacy and response efficacy, norms, social support, relatedness, autonomy, and motivation. SCT constructs address the environment (eg, environmental risks [UV exposure] and settings [health care access]), situation (eg, social norms of risk behaviors), behavior (eg, risk-reduction knowledge and skills), expectations (eg, good health outcomes), observational learning (eg, behavioral modeling), and self-efficacy (eg, confidence to perform prevention) [95]. Three needs must be satisfied when using SDT to foster well-being [94]: (1) competence—ability to control outcomes and feel self-efficacy, (2) relatedness—innate desire to interact with others, and (3) autonomy—need to be in charge of one’s life. Effective interventions implement techniques and strategies that support these 3 basic psychological needs. In need-supportive environments and contexts, extrinsic motivation can be transformed into higher-quality, intrinsic motivation, which is linked to positive health behavior change [96].

Posts will also include engagement strategies to encourage user-generated content and incorporate testimonials. The diffusion of innovations theory (DIT) and social network principles [97] explain that social media are uniquely influential because (1) user activity increases dissemination [98] and (2) information spread among social media communities, notably by knowledgeable peers, reduces uncertainty; makes sentiments dominant [65,99]; and motivates collective action [97,100] via social comparison [97,101] and collective identity that stabilizes actions [101]. Social media’s influence is further clarified by transportation theory [102]. According to this theory, personal stories can be more influential than didactic messages and expert advice [103] partly because of the audience’s identification with the characters [104]. Users often share stories on social media.

Digital and media literacy principles, including “active inquiry and critical thinking about mediated messages” [105], will be addressed in the campaign because many emerging adults are not critical media consumers [106]. Strategies to help emerging adults navigate the media landscape, combat echo chambers of misinformation, counterargue critical information, and develop trust in public health voices are imperative [107,108]. Fact-checking and corrections are important strategies for the campaign, but counternarratives, peer correction, factual elaboration, coherence and credibility appeals, media literacy [109-113], eHealth literacy [114], and advice on safe content sharing are also essential for the posts [69,115]. Media literacy interventions have helped health-related decisions and provided skills to combat unhealthy messages across health topics [116-120], suggesting they will make emerging adults “better prepared and willing to take preventive actions recommended by health professionals” [121]. We will convey how to identify media sources, their intentions, and misinformation; conduct web searches; overcome discomfort of new behaviors; converse with others about cancer risks (skills acquisition); highlight benefits to self, family, and friends (positive outcome expectations); and reinforce that they can reduce risks (self-efficacy). We will measure digital and media literacy skills and the level of misinformation (ie, holding inaccurate beliefs) about cancer prevention as mediators.

#### Social Media Posts

Social media posts will contain text with images, infographics, videos, and links to websites or other social media platforms (eg, Instagram and YouTube) from government, health care, news media, and trusted sources. Preferred health content for emerging adults of any gender and various social groups (eg, race, ethnicity, income, education, and living circumstances) will be identified through community engagement methods. Messages will address SCT [93], SDT [94], DIT [97], and media literacy principles [122] described earlier. The posts will be positive, at the seventh-grade reading level, and in English. The posts will cover 5 content areas:

Cancer prevention: posts will address 6 cancer risk factors and various methods to improve them including behavioral skills for risk reduction, benefits of engaging in such behaviors, social support for these efforts, and strategies to minimize the social and financial costs associated with cancer risk reduction. In addition, advice from health care providers will be shared to help individuals overcome barriers to adopting healthier behaviors. Risk-reducing behaviors will be targeted by the posts include increasing MVPA and healthy eating behavior (more vegetables, fruits, and whole grains and less red and processed meats, sugar-sweetened beverages, highly processed foods, and refined grains); decreasing nicotine product use, alcohol intake, and UV exposure (sunburn); and increasing HPV vaccination. Posts will seek to improve several theoretical mediators, including self-efficacy and response efficacy and perceived risk, and to link cancer prevention to personal goals, including compatibility with values, observable benefits, and simplicity. Posts will also address cost of cancer prevention, present descriptive norms related to healthy and unhealthy behaviors, and highlight social support from family, friends, and partners. They will also promote emerging adults autonomy for their own health and decisions to adopt healthy behaviors. Posts will highlight the cancer prevention benefits of these behaviors and other benefits that may motivate emerging adults to adopt risk-reduction behaviors, including appearance (eg, avoiding skin aging), social (eg, reducing alcohol-induced partner violence), financial (eg, cost savings from quitting nicotine products), and disease prevention (eg, cardiovascular health) benefits. We will use a rotation pattern that covers the 6 cancer risk factors in at least 1 post per week and highlights 1 cancer risk factor in a series of posts each week to provide an in-depth intervention.Digital and media literacy skills: media literacy posts will focus on critical thinking, skill acquisition, and misinformation correction. Posts will aim to improve emerging adults’ digital and media literacy competencies related to (1) access, (2) analysis, (3) creation, (4) reflection, and (5) action [122]. Posts will focus on assessing message credibility and quality (eg, authorship [eg, bots], purpose [eg, marketing], construction, and algorithms) and validity (eg, original source identification, images, deep fake videos, and scientific evidence). Differences in storytelling and scientific evidence will be discussed. Marketing messages will be addressed because advertisers (eg, tobacco, alcohol, and tanning industries) reach emerging adults through social media promotions [41]. Even brief exposure to these marketing messages can instill positive attitudes toward the products [123].Responding to misinformation: we will use our best practices to respond to misinformation [124], that is, messages in conflict with scientific and medical information and advice. Misinformation will be identified by monitoring users’ reactions and comments, auditing the media landscape, and responding immediately [125] to forestall it from going viral. We will respond both proactively in the feed and reactively in replies to the comments. Responses will show empathic engagement and acknowledge users’ uncertainty, confusion, or motivations to prevent defensiveness and maintain trust [125]. Posts will then debunk misinformation by fact-checking, providing factual elaboration and coherence appeals with evidence-based sources [110,111], reframing information to fit existing beliefs, using resistance-to-persuasion tactics (2-sided appeals [126,127] and inoculation [128-130]), telling stories that offer personalized advice, presenting credible statistics and science [111,112,131,132], highlighting prevention actions by resistant groups [132], and depicting patient-provider interactions [132].Family and friend communication: emerging adults are expected to reside in several living arrangements, often with other adults, so posts will present prompts to talk with family (eg, parents, siblings, and partners) and friends about cancer prevention (and content from the campaign posts). Posts will focus on skills for active listening, self-disclosure, support, and conflict management.Referral to community resources: a website will be created that contains links to web-based tools and brief interventions to help emerging adults alter cancer risk behaviors, especially those that may be unknown to emerging adults. Examples include quit-smoking services, portals to state vaccination records, tools for managing the multidose HPV vaccination schedule, and fact sheets and guidelines from health authorities. Resources will be identified by the community advisers and maintained by the investigators. A link to this website and its relevant resources will be included regularly in posts.

#### Development of Cancer Prevention Posts

An agile, just-in-time process will be used to create and adapt posts to be responsive to emerging adults and to reflect current events [133]. Investigators will prepare a campaign framework for developing posts, identifying target behaviors for each cancer risk factor and key theoretical principles. Project staff will continuously audit cancer prevention information and misinformation in (1) published literature, government reports, and national surveys; (2) participant comments on posts; (3) quarterly web-based emerging adult focus groups; and (4) advisory board input. The investigators and media developers will revise posts, add emerging themes, and tailor posts to key subgroups. Initially, 3 months of campaign posts will be prepared, with additional posts developed during the campaign, creating a planned adaptive campaign. Social media posts will be written in English because rural emerging adults are the primary target group, with Hispanic and American Indian emerging adults comprising a minority of them. English continues to be the most common language on the internet, especially in the United States [134,135]. Nearly all young adults in the United States are proficient in English, even most foreign-born young adults [136].

To ensure campaign exposure, posts must regularly engage users because the Facebook algorithm presents posts from the private groups more frequently and prominently in participants’ newsfeeds when they engage more with the group’s posts. To achieve high visibility and engagement, we will post twice per day and (1) provide novel, high-interest, useful, and current-event content; (2) adjust for season; (3) link to content from other emerging adults to create descriptive norms; (4) address age differences and cultural barriers and facilitators; (5) use ethnically diverse emerging adult images that can improve health communication [137]; and (6) use formats such as stories, polls, questions and answers, videos, and visuals, and invite comments [58,98,138-141].

The campaign will be pilot-tested with rural emerging adults (N=25) meeting the inclusion and exclusion criteria displayed in Textbox 1 (13/25, 52% female individuals and ethnically diverse). It will contain a feed of 56 campaign posts (2 per day) over 4 weeks, and participants will provide feedback in focus group discussions.

#### Implementation of Social Media Campaign

The social media campaign will be implemented through Facebook private groups. A staff person will serve as the community manager and schedule posts twice a day on all 7 days of the week (1 message in the morning and 1 in the afternoon) to achieve reach [142,143]. In each cohort, emerging adults will receive welcome posts on purpose and ground rules (eg, respect for others) and then receive the ongoing feed delivered in their separate private group so that posts are identical across cohorts, timely, linked to current events and news stories, relevant for seasons, and engaging. We will not start each cohort at the beginning of the feed because it would require adjusting earlier posts to be current, making them dissimilar across cohorts. The community manager will monitor reactions and comments from emerging adults, answer questions, address uncertainty, and correct misinformation [58,124,133]. The community manager will promote peer influence by, for example, (1) recruiting high-frequency emerging adult users to be guest moderators for up to 3 days to schedule posts and reply to comments and (2) hosting Facebook Live events with emerging adult experts (eg, an emerging adult dietitian). If any bullying arises, the community manager will de-escalate it by (1) highlighting empathy and (2) sending direct messages to stop it. If participants leave a group, they will be contacted to see why. Project staff, except the community manager and the project coordinator, will be blinded to the cohort membership.

Facebook’s private group function possesses unique features not found in other social media platforms. These distinctive qualities offer practical methodological advantages and enhance experimental rigor. Facebook remains one of the most popular social media platforms for emerging adults, used by 70% of the population nationally (among which 70% use it daily), with the majority reporting use in nearly all demographic groups, including by age, rurality, race, ethnicity, and income [43]. Thus, nearly all emerging adults will have existing accounts and be familiar with its interface. Other social media place limits on content delivery that would restrict cancer prevention messaging, including by restricting format (eg, YouTube and Instagram mainly use video and images), length (Snapchat and TikTok deliver short videos), and permanence (Snapchat posts last for 24 hours after posting), and they all restrict the ability to link to other web content more than Facebook. Facebook’s private group function will also help ensure that posts appear in users’ feed and will limit access to posts to group members (posts cannot be shared on other social media) to avoid contamination. Finally, Facebook has superior data analytics for tracking exposure to content compared with other platforms.

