The effect of the treatment on each of the primary outcomes will be examined using a linear mixed-effects model for a stepped-wedge design, as outlined by Hussey and Hughes [183] and Li et al [184]. Repeated measures (6 per individual—T_0_, T_1_, T_2_, T_3_, T_4_, and T_5_ in Figure 1) will be regressed on time since the start of the study (“calendar time”) and time since the start of message exposure (“exposure time”), both of which are expressed as categorical variables via dummy codes. Any mediators found to be significantly impacted by the treatment will be subsequently examined as mediators of the treatment effect on the outcomes via formal mediation models. Multilevel mediation models will be fit as described by Preacher [185] using the structural equation modeling program. As moderation tests require a vastly larger sample than tests of main effects [186], we will examine them without conducting null hypothesis significance tests [187]. We will estimate each model, evaluate the effect magnitude as a function of the moderator, construct bootstrap CIs to illustrate uncertainty, and use false discovery rate controls [182,187]. Linear mixed-effects models for hypothesis 1 will be extended to consider effect modification because of cancer risk behaviors, campaign exposure variables, biological sex, and the time of year of data collection (to control for seasonal fluctuations in UV levels, food availability, and alcohol intake).

Finally, behavioral and experiential engagement will be tested for campaign dose response (ie, duration of the campaign) related to cancer risk behaviors. In addition, behavioral engagement with posts (ie, views, reactions, and comments) on certain topics (eg, risk behaviors, media literacy, or family communication) and formats (eg, text, video, or interactive features such as polls) will be examined to determine if they have an impact on campaign effectiveness.

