### Strengths and Limitations

The planned trial has several methodological strengths, including the unique multi-institutional team of investigators with expertise in each of the health behaviors of interest as well as cancer prevention and control; a diverse, rural population; an understudied age group; extensive community engagement; a multirisk factor approach; the use of social media; a rigorous study design; and high dissemination potential. The stepped-wedge design will provide experimental control, reduce error variance, avoid problems with control groups, model campaign dose, and efficiently use resources to recruit and retain the sample. We will recruit from an internet panel rather than from the community to obtain a large sample from the sparsely populated Mountain West. The social media campaign will be based on theories of health behavior change and social media influence. The stepped-wedge design and a multifaceted analysis of campaign engagement will be used to assess campaign dose effects.

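### Later cohorts join a running, adaptive feed, so pooled exposure-time terms mix how long a cohort was exposed with which posts it saw and should not be read as dose-response

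*Protocol article*

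**What the plan says.** Under Randomized Stepped-Wedge Trial Design, four randomised cohorts start at weeks 1, 13, 26 and 39 and receive about 720, 540, 360 and 180 posts. Surveys are at baseline (T0) and weeks 13, 26, 39, 52 and 104 (T1 to T5).

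Under Implementation of Social Media Campaign, participants "receive the ongoing feed delivered in their separate private group so that posts are identical across cohorts", and "We will not start each cohort at the beginning of the feed because it would require adjusting earlier posts to be current". Under Development of Cancer Prevention Posts, the content is meant to change: "Initially, 3 months of campaign posts will be prepared, with additional posts developed during the campaign, creating a planned adaptive campaign". One listed engagement tactic is to "adjust for season".

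Under Hypothesis Testing, each outcome is regressed on dummy-coded calendar time and dummy-coded "time since the start of message exposure". No term that lets the exposure effect differ by cohort or by feed content is described, apart from time of year as an effect modifier in an extension of the model.

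Duration is treated as dose in several places. Cancer Prevention Social Media Campaign says the trial will "compare varying intervention durations (ie, 13, 26, 36, and 52 weeks". The design section presents the stagger as giving varying doses and lists comparison of cohorts with different durations as an advantage. Strengths and Limitations states: "The stepped-wedge design and a multifaceted analysis of campaign engagement will be used to assess campaign dose effects".

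**The concern.** A single 13-week exposure coefficient shared by four cohorts assumes that 13 weeks of campaign is the same thing whenever it is given. Here it is not. Cohort 1's first 13 weeks are roughly posts 1 to 180; cohort 4's are roughly posts 541 to 720, mostly written later, revised after feedback and fitted to another time of year.

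How much campaign is needed is one of the trial's stated questions. If posts improve, or the campaign acts on a seasonal behaviour, the exposure-time coefficients can rise or fall with duration although duration itself does nothing, or they can misstate a real effect of longer exposure.

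**Working it through.** **Plan figures reproduced.**
- Posts: 2 per day × 91 days = 182 per 13 weeks (stated 180); 2 × 7 × 52 = 728 per year (stated about 720).
- Enrolment: 4 × 175 / 0.70 = 1000, as stated. The power analysis concerns one time-averaged effect, so it does not depend on the exposure-time terms.
- Cohort 2: week 13 to week 52 is 39 weeks. 540 posts / 14 per week = 38.6 weeks. A 36-week duration would give 36 × 14 = 504 posts. The listed 36 weeks fits neither the start week nor the post count.

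**Content behind each exposure level (Q1 to Q4 are feed quarters).**
- 13 weeks: Q1 (cohort 1, week 13), Q2 (cohort 2, week 26), Q3 (cohort 3, week 39), Q4 (cohort 4, week 52).
- 26 weeks: Q1–2, Q2–3 or Q3–4.
- 39 weeks: Q1–3 or Q2–4.
- 52 weeks: cohort 1 only.

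**Model for the illustration.** Generalised least squares, 4 cohorts × T0 to T4, calendar dummies plus exposure dummies (9 parameters, rank 9). The within-person correlation is 0.5 and there are 175 completers per cohort, both from Power Analysis. Each survey is taken before the next cohort starts. T5 is left out: each exposure level at week 104 belongs to one cohort only, and with T5 the model has 14 parameters but rank 13. All quarter effects below are assumptions, in SD units.

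**Case A: no duration effect; only the current quarter's feed matters.** Expected terms at 13, 26, 39 and 52 weeks:
- Quarters 0.20 throughout: 0.200, 0.200, 0.200, 0.200. No bias.
- 0.10, 0.15, 0.20, 0.25: 0.151, 0.164, 0.172, 0.175. False gradient +0.024.
- 0, 0.20, 0.20, 0: 0.139, 0.175, 0.176, 0.191. False gradient +0.052.
- 0.25, 0.20, 0.15, 0.10: 0.199, 0.186, 0.178, 0.175. False gradient −0.024.

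The week-52 contrast of cohort 1 with cohort 4 is exactly 0 in all four.

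**Case B: each quarter seen adds its own lasting effect.** Pooled gradient (52 minus 13 weeks), then the true week-52 difference between cohorts 1 and 4:
- 0.05 in every quarter: 0.150 and 0.15.
- 0.08, 0.06, 0.04, 0.02: 0.181 and 0.18.
- 0.02, 0.04, 0.06, 0.08: 0.119 and 0.12.
- All 0.20 in Q1: 0.179 and 0.20.
- All 0.20 in Q2: 0.250 and 0.20.
- All 0.20 in Q3: 0.171 and 0.20.
- All 0.20 in Q4: 0 and 0. Every cohort gains equally by week 52, so starting early brings nothing.

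**Precision at 175 per cohort.**
- Pooled 13-to-52-week gradient: standard error 0.082 SD.
- Week-52 contrast of two cohorts, adjusted for T0: √(2 × (1 − 0.5²) / 175) = 0.093 SD.
- Ratio 0.0926 / 0.0823 = 1.13.

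**Can content be separated from duration?** Exposure dummies plus additive quarter effects on T0 to T4 give 13 parameters but rank 11, and neither set is separately estimable. Over T0 to T3, where an unexposed cohort remains, a separate effect for each of the six exposed cohort-by-survey cells is estimable (10 parameters, rank 10). Adding T4 loses this (15 parameters, rank 14).

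**The case against.** The case against has real force.

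- *Joining a running feed is disclosed and justified.* This stands. Restarting the feed would have meant altering posts, and nothing here asks for that.
- *Mitigations exist.* Calendar dummies remove additive season and secular effects; the six risk factors are rotated weekly; time of year is examined as a modifier. This stands in part. A campaign effect that itself varies by quarter is not additive, and the illustrations already include the calendar dummies. Rotation balances topics but not quality, season or topical content. With one feed, time of year follows the calendar period, so the modifier cannot separate content from duration.
- *The size is small.* This stands: 0.02 to 0.05 SD is about 0.3 to 0.6 standard errors of the gradient.
- *The week-52 contrast does not isolate duration either.* This stands. Cohort 1 has seen all four quarters and cohort 4 only the last, so longer exposure also means different posts. What the contrast does give is an unbiased, randomised estimate of starting this feed early rather than late, in every scenario run. The pooled gradient does not.
- *The protocol does not call the pooled coefficients a dose-response.* A reader might infer that it does, because exposure time is in the main model and duration is repeatedly called dose. The text does not go that far: those terms are introduced for the treatment effect, the dose-response sentence is about engagement, and the design section already speaks of comparing cohorts. The point is therefore to fix which quantity answers the duration question.

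**Conclusion.** The point holds as a limit on interpretation. Exposure time is pooled over cohorts that saw different posts in different seasons, and the protocol regards duration as dose. If the campaign effect varies by feed quarter, the pooled terms can show a modest false gradient or distort a true one, by about 0.02 to 0.05 SD in most of the unequal-quarter illustrations and less under smooth cumulative trends. If all quarters work equally well, there is no error. The sizes rest on assumed quarter effects, correlation 0.5 and 175 completers per cohort.

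A reader might infer that the trial's main result is compromised. The documents do not support that: comparison of exposed with not-yet-exposed cohorts still rests on randomisation, the stated primary evaluation is of the campaign as a whole, and the sample size was set for a time-averaged effect. The 36-week figure is a separate, plain inconsistency.

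**What to change.** - Define the duration comparison as the randomised contrast of the four cohorts at week 52 (T4), adjusted for the T0 value, and repeat it at week 104 for persistence.
- State that it estimates the effect of starting this feed earlier, meaning more posts and also the earlier posts, and that duration and content cannot be separated in this design.
- State that the pooled exposure-time coefficients will not be interpreted as dose-response.
- As a sensitivity analysis, let the exposure effect vary by feed quarter over T1 to T3, where unexposed cohorts remain.
- Reconcile the 36 weeks under Cancer Prevention Social Media Campaign with the week-13 start and 540 posts under Randomized Stepped-Wedge Trial Design.

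This changes analysis wording only and needs no new data. The price is a standard error about 13% larger for the duration contrast (0.093 against 0.082 SD). The week-52 contrast also cannot show a benefit that all cohorts gain equally in the last quarter.
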